### Physician recruitment and training

A one-day training session was provided to all physicians involved in the study to standardize how to initiate methadone treatment (as set down by the trial’s guidelines) and to become acquainted with the design of the trial. This training session also provided the opportunity to collect data about the physicians’ own socio-demographic characteristics and their history of care with opioid-dependent individuals.

We trained 57 prescribers and each site was characterized by a group of trained primary care physicians and a group of trained physicians from a CSAPA. Primary care and CSAPA physicians collaborated closely together to make the randomization process possible and to ensure effective patient follow-up. Concerning patient selection, the Mini-International Neuropsychiatric Interview (MINI) was used to ascertain DSM-IV diagnosis
[14] of substance disorders in order to exclude patients with alcohol-benzodiazepines co-dependence. It has been already shown that such patients require closer follow-up
[15] and are at greater risk of overdose
[13]. During pre-trial training, physicians learned how to use the MINI and familiarized themselves with the trial’s guidelines, including details on the protocol. They also received a manual on drug-drug interactions
[16]. One of the main goals of the training session was to remind physicians about the pharmacokinetic profile of methadone during induction i.e. its slow and progressive plasma scale-up before reaching a steady-state. For example the trainer commented that: “An excessive dose given on Monday may lead to an overdose only on Thursday”. The session also helped physicians to identify patients with a high risk of overdose. Furthermore, it emphasized the importance of the information physicians needed to provide patients when initiating methadone. A trial-specific information booklet designed for the patient was drafted explaining the study protocol, all the risks and benefits of initiating methadone, how to deal with complicated or unexpected issues such as travel and holidays, effects on one’s desire to become pregnant, as well as information on intoxication, overdoses (e.g. how to recognize overdose symptoms) and other side effects.

### Pharmacist involvement

We also enrolled primary care pharmacists who agreed to deliver methadone and supervise dose taking during the 2-week induction phase (except during weekends, in most cases) for all the trial’s participants. Pharmacists were asked to complete a self-administered questionnaire before and after the trial and also to register all stock entries and exits for methadone doses.

### Remuneration

Physicians who accepted to participate in the trial were remunerated for the one-day initial training session and for each medical visit during the induction phase. Participants were covered for all health costs related to their methadone induction.

### Intervention

#### Patient screening

The first visit took place when a patient willing to be treated for his/her opioid dependence came to a Methaville physician, either in primary care or in a CSAPA (see Figure
1). During this visit, the physician explained the study protocol to the patient and performed the trial screening to confirm the patient’s eligibility. If he/she was eligible to enter the study and provided written informed consent to participate, the physician then immediately called the centre of methodology and management (CMM) of unit U912 to randomize the patient into one of the two groups. Details were exchanged and at the end of the medical visit the participant knew where he/she had to initiate methadone: in primary care or in a CSAPA.

This study was approved by the Ethics Committee of Persons Protection in Paris, France.

The screening physician, whether in a CSAPA or in a primary care setting, provided the randomization setting to the patient: if the patient was randomized into the same type of setting at that where initial screening took place, he/she could initiate methadone where he/she was screened. Otherwise he/she had to go to the other type of setting.

#### Methadone initiation

During the induction period, the selected physician for the methadone induction had to adjust the methadone dose until stabilization was reached. This induction period was crucial and required a great deal of attention by both the physician and the patient in order to reach a balance between overdose risk reduction and withdrawal symptoms’ alleviation. The initial methadone prescription could not be above 40 mg a day. After writing this first prescription, the physician was required to call the local pharmacist where the patient had chosen to take the methadone. The patient was then given the prescribed dose (in syrup form) at the pharmacy and had a medical visit 2 or 4 hours after that intake in order to assess the tolerance of the first prescribed dose. During the induction period, the patient had to see the physician at least twice a week after the initial prescription consultation. Depending on the severity of opioid dependence, the first dose prescribed could increase by 10 mg every 2 to 4 days with a medical visit 48 hours after each dose increase.

#### Maintenance phase

After the initial 14 days, the participant could choose to remain in the allocated prescription setting or to change to the other one (i.e. to primary care or CSAPA).

The possible risks for participants were methadone side effects, which are the same as those encountered in standard clinical care: drowsiness, sweating, constipation, sleeping and libido disorder
[17]. The potential benefit for patients initiating in primary care was that they would have the chance to initiate methadone in primary care, something not currently possible in the standard system of care.

As there is an increased risk of overdose until stabilization of doses is reached, special guidelines for methadone prescription were drawn up and used, both to train physicians and to have standardized guidelines throughout the course of the trial.

#### Lost to follow-up

During the induction phase (from day 0 to day 14), the patient had to:

(1) regularly go to the pharmacy (according to the scheduled date of prescription refill) during opening hours to take the treatment. If he/she didn’t appear there for more than 48 hours, the pharmacist had to inform the centre of methodology and management (CMM) which in turn contacted the participant.

(2) see the physician for the scheduled medical visit, every 72 hours on average. If this appointment was not observed, the physician had to call the CMM.

If after 24 hours of investigation, the CMM still could not find the participant in either of these two cases, he/she was considered as “lost to follow-up”. The CMM had to then contact the centre of evaluation and information on drug dependence (CEIP) to check that the participant had not had an overdose.

#### Safety

An independent data and safety monitoring board periodically reviewed the trial’s efficacy and safety data. This safety committee comprised several experts in the field including addiction psychiatrists, forensic scientists, pharmacologists, methodologists and institutional scientists.

Stopping rules were based on occurrence of overdoses and severe adverse effects. 

### Objectives

The trial is nearing completion. Its primary objective is to demonstrate the non-inferiority of the proportion of individuals abstinent from street opioids after one year of methadone in patients inducted in primary care with those inducted in CSAPA. Patients who initiated methadone in primary care are expected to have better outcomes compared with those in CSAPA in terms of retention, quality of life and satisfaction after 1 year of methadone treatment.

### Outcomes and instruments

Multiple sources were used for data collection at screening (week preceding recruitment and first/seventh day after recruitment), at recruitment (day zero or month zero), induction (from the first to the second week of treatment) and maintenance (third, sixth and twelfth months). Data collection methods (ongoing) include face-to-face interviews, phone interviews using a Computer Assisted Telephone Interview
[18] and self-administered questionnaires, all adapted and validated for the type of information to be gathered.

The Opiate Treatment Index (OTI), a multi-dimensional questionnaire based on patients’ self-report
[19] is being used to measure Methaville’s primary outcome. This consists in measuring the proportion of all participants abstinent from street opioids after 1 year of treatment. Some secondary outcomes are also measured. First, retention in treatment and occurrence of overdoses are assessed. The prevalence of other HCV risk transmission practices is also documented using a series of questions extracted from a standardized questionnaire specifically adapted for this purpose - the Blood-Borne Virus Transmission Risk Assessment (BBV-TRAQ)
[20,21] - and also the questionnaire used by Lucidarme et al. in their longitudinal study
[22,23]. Other data about indicators relevant for the purpose of this study have been collected: depressive symptoms (using the CES-D questionnaire
[24]), suicidal risk (the Beck Hopelessness Scale
[25]), impulsivity (the Barratt Impulsiveness Scale), sensation seeking (the Brief Sensation Seeking Scale (BSSS)
[26]), tobacco dependence (the Fagerstrom test
[27]), alcohol consumption (the AUDIT questionnaire
[28]), pain assessment (the Brief Pain Inventory
[29]), adherence to methadone prescription, patient-health care provider relationship
[30], opioid withdrawal (the subjective opioid withdrawal symptoms scale (SOWS)
[31]), quality of life (the 12-item Short-Form Health Survey (SF-12)
[32]), Attention Deficit Hyperactivity Disorder (Adult ADHD Self-Report Scale 6 item version
[33]), urinary drug screening, and finally socio-demographic information on history of incarceration and contact with associations. Quality assurance and data security measures were established and approved for this protocol on the 21^st^ of May 2008.

### Sample size

We used the proportion of all patients abstinent from street opioids after 1-year of methadone treatment for the sample size. Many studies have shown that 60% to 80% of opioid-dependent individuals treated with methadone completely stopped using street opioids after one year of treatment
[34-36]. The hypothesis for this study was that after one year of methadone treatment, the proportion of patients not using opioids in CSAPA would be 70%. Considering a margin of inferiority of 15% in the primary care arm, 200 patients needed to be recruited to investigate non-inferiority.

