**Methods/Design:**

The ANRS-Methaville study is a randomized multicenter non-inferiority control trial comparing methadone induction (lasting approximately 2 weeks) in primary care and in CSAPA. The model of care chosen for methadone induction in primary care was based on study-specific pre-training of all physicians, exclusion criteria and daily supervision of methadone during the initiation phase. Between January 2009 and January 2011, 10 sites each having one CSAPA and several primary care physicians, were identified to recruit patients to be randomized into two groups, one starting methadone in primary care (n = 147), the other in CSAPA (n = 48). The primary outcome of the study is the proportion of participants abstinent from street opioids after 1 year of treatment i.e. non-inferiority of primary care model in terms of the proportion of patients not using street opioids compared with the proportion observed in those starting methadone in a CSAPA.

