### Research design

This study is a multi-site, open-label, randomized controlled non-inferiority trial, comparing methadone induction in France in a CSAPA or with primary care physicians with an allocation ratio of 1 :2. The randomization procedure allocated patients to the two different types of prescriber for methadone induction, lasting approximately 14 days for both prescribers).

A pilot phase was first carried out at one site (Avignon CSAPA and local primary care physicians) at a “slowed” recruitment rate in order to identify and prevent possible future problems when the trial was extended to the other sites.

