### Statistical methods

The trial was initially designed as a non-inferiority trial aimed to show the non-inferiority of the proportion of *non-injectors* who started methadone in primary care compared to those who started it in a CSAPA. However, as the number of patients injecting opioids at recruitment was low, the primary outcome was changed as ‘the proportion of *patients abstinent from* of street opioids after 1 year’, and the dimension of the study was re-computed. These changes were approved by the Scientific Committee of the trial, the Independent Committee and the Ethical Committee (CPP).

Secondary outcomes are the occurrence of fatal and non-fatal overdoses and the percentage of retention in both arms. We also investigated the prevalence of other HCV transmission practices and the effectiveness of treatment in terms of adherence, social insertion, addictive behaviours, quality of life, psychiatric comorbidities, social insertion, reduction in criminal acts and cost effectiveness.

When data analysis is completed later in 2012, the computation of the 95% confidence interval for the proportion of patients abstinent from street opioids at M12 in the two arms will be based on Intention To Treat (ITT), with lost to follow-up considered as a therapeutic failure (opioid users). Additional analyses will be performed without ITT, focusing on the most recent available information about opioid use during treatment. Mixed generalized linear models analyses will be used to identify predictors of the different outcomes. Non-inclusion or non-termination biases will be controlled for using selection models - including Heckman type models
[37] - and other approaches to take into account for the drop out process
[38].

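### The 200 patients said to be needed give only about 59–64% power for the planned 95% interval at 1:2 under equal true rates, and the reported 48/147 split gives about 50–58%

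*Protocol article*

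**What the plan says.** The Sample size section of the protocol article bases the calculation on one-year abstinence among all patients. It cites studies giving 60% to 80% and adopts the hypothesis that "the proportion of patients not using opioids in CSAPA would be 70" per cent. It continues: "Considering a margin of inferiority of 15% in the primary care arm, 200 patients needed to be recruited to investigate non-inferiority". No power, alpha, assumed primary-care rate or dropout allowance accompanies the figure.

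The other inputs stand elsewhere in the article:

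- Research design compares induction in a CSAPA or "with primary care physicians with an allocation ratio of 1 :2", that is, one CSAPA patient for every two in primary care.
- Statistical methods plans a 95% confidence interval for month-12 abstinence in the two arms by intention to treat, "with lost to follow-up considered as a therapeutic failure (opioid users"). It also says that the study's size was recalculated when the primary outcome was changed.
- The abstract reports the groups as "one starting methadone in primary care (n = 147), the other in CSAPA (n = 48"), 195 in all and closer to 1:3 than to 1:2.

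**The concern.** A reader takes a statement that 200 patients were needed to mean that 200 gives a good chance of showing non-inferiority if the settings are equally effective. The article's own rate, margin, ratio and confidence level do not bear that out.

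This is the primary comparison, and the abstract's discussion says the result may lead to a change in methadone's licensing. If the true rates are equal and the trial still misses its margin 42–50% of the time at the reported arm sizes, a miss says little about primary care. Without a stated power and an agreed reading of a miss, it could be taken as evidence against primary-care induction.

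**Working it through.** **Inputs**

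- CSAPA rate 70% and margin 15%, read as 15 percentage points (Sample size).
- Allocation 1:2 (Research design); reported arms 48 and 147 (abstract).
- 95% confidence level (Statistical methods), read as a two-sided interval for the difference, hence one-sided 2.5%.
- Assumed because not stated: equal true rates of 70%, and 80% as a conventional power.
- No inflation for loss, since lost patients stay in the denominator.

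**1. Trying to reproduce 200**

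n(CSAPA) = (z_alpha + z_beta)² × 0.70 × 0.30 × (1 + 1/r) / 0.15², where r is primary-care patients per CSAPA patient.

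- One-sided 2.5%, 80% power, r = 2: (1.960 + 0.842)² × 0.21 × 1.5 / 0.0225 = 7.849 × 14 = 109.9, so 110 + 220 = **330**.
- The same with r = 1: 147 + 147 = **294**.
- One-sided 5%, 80% power, r = 2: (1.645 + 0.842)² × 14 = 86.6, so 87 + 174 = **261**.

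At 90% power and one-sided 2.5% the totals are 444 (1:2) and 394 (1:1). None of these is near 200.

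Without dropout inflation, these settings come close:

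- one-sided 5%, 70% power, 1:2: (1.645 + 0.524)² × 14 = 65.9, so 66 + 132 = 198;
- one-sided 5%, 75% power, 1:1: 202;
- one-sided 10%, 85% power, 1:1: 202. At 80% power and 1:2, one-sided 10% gives 192.

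A few further matches need an unstated dropout allowance. The only one at 80% power is one-sided 10%, 1:1, 15% dropout (200). No match uses the planned 95% interval at 80% or 90% power.

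**2. Power for the stated size and for the reported arms**

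SE = sqrt(0.21/n1 + 0.21/n2); power = Phi(0.15/SE − 1.96).

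- 67/133: SE = sqrt(0.003134 + 0.001579) = 0.0687; 0.15/SE = 2.185; power = Phi(0.225) = **58.9%**; half-width 1.96 × 0.0687 = 13.5 points.
- 48/147: SE = sqrt(0.004375 + 0.001429) = 0.0762; 0.15/SE = 1.969; power = Phi(0.009) = **50.4%**; half-width 1.96 × 0.0762 = 14.9 points.

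At 48/147 with the Wald interval, primary care must therefore be observed essentially level with CSAPA (difference above about −0.1 point).

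**3. Sensitivity**

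| Setting | 67/133 | 48/147 |
|---|---|---|
| Exact binomial, Wald limits | 59.1% | 50.7% |
| Farrington-Manning | 62.9% | 57.1% |
| Exact binomial, Newcombe limits | 64.3% | 58.4% |
| One-sided 5%, Wald | 70.5% | 62.7% |
| Common rate 60% to 80%, Wald | 53–71% | 45–62% |
| Margin relative (10.5 points), Wald | 33% | 28% |
| Primary care 75% against 70%, Wald | 84% | 76% |

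Only the last row reaches 80%, and only at 67/133. A 4-point advantage (74% against 70%) gives 80% at 67/133: SE = sqrt(0.003134 + 0.74 × 0.26/133) = 0.0677; 0.19/0.0677 = 2.807; Phi(0.847) = 80%.

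**The case against.** The strongest reply is that no stated calculation is shown to be wrong. The article gives a rate, a margin and a total. Power, alpha and the primary-care rate are supplied here, and an article may leave them to the full protocol. Nor does Statistical methods name an interval for the difference or a one-sided level. This stands in part. A reader might infer that 200 is an arithmetic error, and the article does not support that, because about 200 can be reached with settings it does not state. The mismatch with the planned 95% interval at any conventional power under equal rates remains. Even a one-sided 5% test leaves power at about 70%.

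Primary care might have been assumed better. An advantage of 4–5 points would give 80–84% power at 1:2, and since lost patients count as failures, better retention could raise the primary-care rate. But Objectives expects better retention, quality of life and satisfaction; for abstinence it states only non-inferiority.

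Two further inferences should not be drawn:

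- **That the expected rate must be below 70% because lost patients count as opioid users.** Sample size says it is based on all patients, so the 70% cannot be shown to be a rate among completers. The article gives no expected loss.
- **That the 147/48 split shows the planned size was miscalculated.** It shows only the power achieved; the planned size has to be judged at 1:2.

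Finally, recruitment is over and the reported interval will show its own precision. That limits what can be changed, but not the value of stating the power correctly.

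**Conclusion.** The concern holds in this limited form. Under equal true rates of 70%, an absolute 15-point margin and a two-sided 95% interval for the difference, 200 patients at 1:2 have about 59% (Wald) to 64% (Newcombe) power. About 330 would be needed for 80%. The reported 48/147 has about 50–58% power, with an expected half-width of about 15 points, roughly the whole margin.

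The conclusion depends on the reading of the interval and on equal rates, neither of which the article spells out. It does not depend on the interval method, on the choice between one-sided 2.5% and 5%, or on the common rate within the cited 60–80%: each leaves power below 80%. It would change if primary care had been assumed about 4–5 points better for abstinence, which the article does not say.

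**What to change.** Before unmasking, which Blinding places after the last month-12 interview, restate the sample-size paragraph:

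1. Give the alpha or confidence level, the target power and the primary-care rate actually used, with the margin as 15 absolute percentage points and the allocation ratio.
2. Report the achieved power at 48/147 (about 50–58% under equal rates) and the expected 95% half-width (about 15 points).
3. State how the interval for the difference (primary care minus CSAPA) will be read. Non-inferiority is shown if the lower limit lies above −15 points. The result is inconclusive if the interval crosses −15. Inferiority beyond the margin is concluded only if the whole interval lies below −15.

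The cost is a rewritten paragraph and a less favourable stated power. No extra patients are needed.

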### Randomization

For allocation of the participants to a primary care or a CSAPA physician, a computer-generated list of random numbers was used within a secured centralized internet system. Randomization sequencing was not stratified by the CMM, which generated the randomization sequence by computer and provided the number by phone to the prescribing physicians when recruiting a patient into the study.

### Blinding

By definition, the arm could not be masked from the prescribing physician but it was masked from all the scientific team involved in the trial. It was obviously unmasked to the logistics team who conducted the interviews and to statisticians and the data managers of the research group, because they had to regularly meet and submit reports to the Independent Committee of the trial. The study will be unmasked at the end of the last M12 interview, during the course of 2012.

### Statistical methods

The trial was initially designed as a non-inferiority trial aimed to show the non-inferiority of the proportion of *non-injectors* who started methadone in primary care compared to those who started it in a CSAPA. However, as the number of patients injecting opioids at recruitment was low, the primary outcome was changed as ‘the proportion of *patients abstinent from* of street opioids after 1 year’, and the dimension of the study was re-computed. These changes were approved by the Scientific Committee of the trial, the Independent Committee and the Ethical Committee (CPP).

Secondary outcomes are the occurrence of fatal and non-fatal overdoses and the percentage of retention in both arms. We also investigated the prevalence of other HCV transmission practices and the effectiveness of treatment in terms of adherence, social insertion, addictive behaviours, quality of life, psychiatric comorbidities, social insertion, reduction in criminal acts and cost effectiveness.

When data analysis is completed later in 2012, the computation of the 95% confidence interval for the proportion of patients abstinent from street opioids at M12 in the two arms will be based on Intention To Treat (ITT), with lost to follow-up considered as a therapeutic failure (opioid users). Additional analyses will be performed without ITT, focusing on the most recent available information about opioid use during treatment. Mixed generalized linear models analyses will be used to identify predictors of the different outcomes. Non-inclusion or non-termination biases will be controlled for using selection models - including Heckman type models
[37] - and other approaches to take into account for the drop out process
[38].

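### Scoring every lost patient as an opioid user in both arms is not reliably conservative for non-inferiority, and no drop-out analysis is tied to the conclusion

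*Protocol article*

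**What the plan says.** Objectives: "Its primary objective is to demonstrate the non-inferiority of the proportion of individuals abstinent from street opioids after one year of methadone", comparing primary-care induction with CSAPA induction. The same section adds a directional expectation: "Patients who initiated methadone in primary care are expected to have better outcomes compared with those in CSAPA in terms of retention". Two patient-reported outcomes are named there as well.

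Sample size: the plan assumes that "the proportion of patients not using opioids in CSAPA would be 70" per cent, and sets the margin with the words "Considering a margin of inferiority of 15% in the primary care arm".

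Statistical methods: the primary result is "the computation of the 95% confidence interval for the proportion of patients abstinent from street opioids at M12" in the two arms, by intention to treat, "with lost to follow-up considered as a therapeutic failure (opioid users". The rule is the same in both arms. Additional analyses drop intention to treat, "focusing on the most recent available information about opioid use during treatment". The section also plans selection models, including Heckman-type models, and other approaches to drop-out. It does not say what part any of these plays in the non-inferiority conclusion. The article gives no expected loss rate and does not itself call the rule conservative.

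**The concern.** Counting missing patients as failures is often thought of as cautious. That intuition comes from superiority trials, where a diluted difference works against the claim. Here the claim is that primary care is not much worse, so dilution works for it.

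The rule adds failures to each arm in proportion to that arm's loss. If the failures wrongly added are more frequent in CSAPA, an abstinence deficit in primary care looks smaller than it is. The article expects better retention in primary care. As far as retention in treatment and follow-up at M12 move together, that expectation points in the anti-conservative direction. The Abstract and Discussion say that the result may change the conditions under which methadone can be started, so the primary interval should not depend on an untested assumption about the lost.

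**Working it through.** **Inputs from the article**
- Margin 15% (Sample size), read as 15 percentage points.
- CSAPA abstinence 70% (Sample size). A true deficit exactly at the margin is then 70% v 55%.
- 48 CSAPA and 147 primary-care patients (Abstract).
- A 95% interval (Statistical methods).

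**Assumed, because the article gives no figure:** the loss rates, abstinence among the lost, and the decision rule. Non-inferiority is taken as declared when the lower two-sided 95% Newcombe limit for primary care minus CSAPA lies above −15 points. Probabilities are exact binomial sums. The plan states no figure of its own to reproduce on this point, and its total of 200 is not an input.

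**Formula.** Let L be an arm's loss rate, q the true abstinence among its lost patients, and P the true abstinence in all its randomised patients. Scored abstinence is P − L·q. So

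scored deficit = true deficit − (L_CSAPA·q_CSAPA − L_PC·q_PC).

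The sign of the bracket decides everything:
- Positive: the deficit shrinks, which is anti-conservative.
- Zero: no effect. This holds if every lost patient uses (both q = 0), or if L and q are equal across arms.
- Negative: conservative.

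**Example, 30% v 20% loss, 20% of the lost abstinent in both arms.** Scored abstinence is 70 − 0.30×20 = 64.0% and 55 − 0.20×20 = 51.0%, so the deficit is 13.0 points.

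**Example, 30% v 20% loss, lost patients half as likely to be abstinent as followed patients.** Abstinence among the followed is P/(1 − 0.5L): 0.70/0.85 = 82.4% and 0.55/0.90 = 61.1%. Scored abstinence is 82.4×0.70 = 57.6% and 61.1×0.80 = 48.9%, so the deficit is 8.8 points before rounding.

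**Results, true deficit 15 points throughout**

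| Loss CSAPA / primary care | Abstinence among the lost | Scored CSAPA v primary care | Scored deficit | False non-inferiority |
|---|---|---|---|---|
| 0 / 0 | – | 70.0 v 55.0 | 15.0 | 2.9% |
| 30 / 30 | 20% in both | 64.0 v 49.0 | 15.0 | 2.8% |
| 20 / 20 | as followed in own arm | 56.0 v 44.0 | 12.0 | 6.2% |
| 30 / 30 | as followed in own arm | 49.0 v 38.5 | 10.5 | 8.4% |
| 30 / 20 | none | 70.0 v 55.0 | 15.0 | 2.9% |
| 30 / 20 | 10% in both | 67.0 v 53.0 | 14.0 | 3.8% |
| 30 / 20 | 20% in both | 64.0 v 51.0 | 13.0 | 4.9% |
| 30 / 20 | half as likely as followed | 57.6 v 48.9 | 8.8 | 12.8% |
| 30 / 20 | as followed in own arm | 49.0 v 44.0 | 5.0 | 24.3% |
| 20 / 30 | as followed in own arm | 56.0 v 38.5 | 17.5 | 1.3% |

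**Cross-check.** An unpooled Wald approximation at 48/147 gives 2.5% with no loss and 22.5% for 30/20 with the lost like the followed. At 67/133 (200 patients split 1:2) the latter is 26.7%. The pattern depends on neither the interval method nor the split.

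**Caution on the low-q rows.** With overall CSAPA abstinence held at 70%, 10 to 20% abstinence among a lost 30% implies 67/70 = 96% down to 64/70 = 91% among those followed. These rows are possible but need very high abstinence in followed CSAPA patients.

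**The case against.** Much of the opposing case stands.

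- **Missing counted as using is interpretable.** In opioid dependence it is a recognisable definition of failure, and if all the lost do use, there is no bias. This is a good reason to keep the rule, but not to leave the assumption untested.
- **Inflation is not general.** A reader might infer that the error rate rises whenever some lost patients are abstinent. It does not: with 30% loss in each arm and 20% of the lost abstinent in both, the rate is 2.8%.
- **The large figures need a strong assumption.** The 24% needs both more loss in CSAPA and lost patients who do as well as those followed. Nothing in the article supports the latter for patients who disappear.
- **Retention is not follow-up.** The article expects better retention in treatment, which is a separate secondary outcome. Some data come from telephone interviews, and people who could not be reached by phone were excluded. A patient who left methadone but was interviewed at M12 is not lost.
- **Drop-out is not ignored.** The planned selection and drop-out models address informative loss directly. What remains is that nothing links them to the non-inferiority conclusion. The one supporting analysis described in concrete terms lets an earlier on-treatment report stand for M12.

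Two further readings are tempting, and the article does not support them. The Lost to follow-up section ("If after 24 hours of investigation, the CMM still could not find the participant in either of these two cases") might be taken to make an induction-phase flag a failure even if the patient is interviewed at M12. That section is an overdose-safety trigger for days 0 to 14, and nothing says that it overrides an observed M12 outcome. A reader might also call the lack of a per-protocol agreement rule a defect. Such a rule is debatable and is commonly left to the analysis plan, which is not shown.

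**Conclusion.** The point holds in a limited form. The article fixes, as the primary non-inferiority analysis, a rule whose direction of bias depends on unknown quantities: loss and abstinence among the lost, by arm. It is anti-conservative when the product of the two is larger in CSAPA, neutral when the products are equal, and conservative when the product is larger in primary care.

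For a true deficit at the margin and an assumed 30% v 20% loss, the false non-inferiority rate runs from 2.9% (no lost patient abstinent) through about 4 to 5% and 13% to 24%. Reversing the loss to 20% v 30%, with loss unrelated to use, gives 1.3%. All loss rates and all abstinence rates among the lost are assumptions. The expected retention advantage makes the unfavourable direction plausible, but does not establish it. The documents do not support a claim that the rule is biased toward non-inferiority in general, or that a positive result would merely reflect retention.

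**What to change.** In Statistical methods:

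1. Keep lost = failure as the primary analysis, and state that it applies to patients with no M12 outcome.
2. Report the number and proportion with no M12 outcome by arm, beside the primary result.
3. State that non-inferiority will be called robust only if it also holds when M12 abstinence is multiply imputed in all randomised patients from baseline, M3 and M6 Opiate Treatment Index data, and urine results.
4. Add an arm-specific tipping-point analysis to that imputation. Its grid should include the case in which lost primary-care patients are users and lost CSAPA patients are abstinent at their arm's observed rate.
5. Make this the main supporting analysis, in place of the one based on the latest available information. The planned selection and drop-out models can stay as further sensitivity analyses.

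Cost: some additional analysis on data that the article already lists as collected, with no new visits or patients. Non-inferiority becomes somewhat harder to claim. The article places the analysis in the future, so the rule can be fixed before the M12 comparison is made.
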